### Criteria for eligibility

Participants aged 18–80 years of both sexes.

#### Inclusion.

Patients previously diagnosed with HF by a cardiologist using the European Society of Cardiology (ESC) recommendations [4].Patients with an indication for exercise.Patients with electronic devices such as computers, tablets, or mobile phones.Participants who accept and sign the informed consent form.

#### Exclusion.

Patients with respiratory comorbidity or any limitation to perform active and resistive movements (recent fractures, recent hemodynamic changes, coronary artery disease event after diagnosis of cardiovascular disease, infectious diseases, and neuromuscular limitations).

### Outcomes measures (dependent variables)

#### Functional aerobic capacity.

The distance covered in the 6MWT will be taken into account [10,11], with distances between <350m and <200m considered as risk factors [12]. It will be performed in a 30 m corridor with two cones at the ends to define the distance to be walked. Before the start, each patient will be stimulated to walk as fast as possible. The remaining time will be displayed for each minute elapsed, Therefore, two attempts of this test will be conducted, and the most significant distance, meaning the greatest distance, will be recorded. Participants will have a rest period between each attempt to return to their baseline state before starting the test again. Considering SpO2, HR, and blood pressure variables. The latter will be measured with a sphygmomanometer and aneroid sphygmomanometer (WelchAllyn® DS44−11CBT).

The 1-minute sit-to-stand repetitions will be performed with the patient seated. From an upright position in a chair against a wall at a standard height of 46 cm without armrests, the patient will have to stand and sit for 1 minute as quickly as possible [13]. The Duke Activity Status Index (DASI) functional capacity questionnaires [14] will be administered, with a score of <4 considered as a risk point [15].

#### Clinical variables.

These will be obtained from the initial measurements at enrollment in the CR program, a structured interview, and the patient’s medical history. Risk factors, symptoms, anthropometry (body mass index, abdominal circumference, fat percentage, water percentage, lean mass), left ventricular ejection fraction (LVEF), total cholesterol, high-density lipoprotein (HDL), low-density lipoprotein (LDL), triglycerides, and reason for leaving the program will be taken into account. The accepted values in cardiovascular patients of total cholesterol <200mg/dl, LDL < 100 mg/dl, HDL in men > 40 mg/dl, women >50 mg/dl, and triglycerides 150 mg/dl will also be considered [16].

#### Anxiety and depression.

The Hospital Anxiety and Depression Scale (HADS) is a self-administered instrument that measures symptoms of depression and anxiety in people without a psychiatric diagnosis. The scale score ranges from 0 to 21. It is scored on a Likert scale from 0 to 3: the higher the score, the greater the intensity or severity of symptoms [17]. The Patient Health Questionnaire 9 (PHQ-9) is a questionnaire that measures the presence and severity of depressive symptoms. It is widely used in primary care settings. It consists of the nine symptoms of depression according to the DSM-IV20 criteria [18].

#### Health-related quality of life.

HRQoL will be assessed using the Minnesota Living with Heart Failure Questionnaire (MLFHQ). It is an instrument used to know the quality of life of patients with HF and provides information for two dimensions, physical and emotional, in addition to the total score [14].

#### Independent variables.

The variables considered will be age, sex, marital status, health system, occupation, level of education, and socioeconomic strata (in Colombia, strata 1, 2, and 3 correspond to low strata, which include users with fewer resources who are beneficiaries of public utility subsidies. Strata 4, 5, and 6 correspond to high strata, which include users with more significant economic resources), sessions completed, weeks in the program, and percentage of adherence.

### Assignment of intervention

Intervention allocation will be randomized using the block and sealed envelope method. The investigators will prepare the envelopes. After patients have consulted with the specialist, a person unaffiliated with the research will ask them to select one of the envelopes for subsequent planning of the intervention process. This will maintain blinding of the assessors and investigators.

If a patient assigned to telerehabilitation drops out, unmasking will occur. As a result, a place in the experimental group to which the patient belonged will become available, and the patient will continue the rehabilitation sessions as usual. This will be the case for those assigned to telerehabilitation.

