## Introduction

Cardiovascular diseases (CVDs) are a significant public health problem worldwide and are considered the leading cause of preventable illness, disability, and mortality [1]. In Latin America and the Caribbean, CVDs are the leading cause of death from chronic non-communicable diseases. There are about 726,000 deaths per year, and these figures are increasing, being one of the leading causes of years lost in people [1]. Heart failure (HF) is one of the CVDs, so the incidence, prevalence, decline in quality of life, frequent hospitalizations, morbidity, and mortality associated with this disease are high, and chronic patients often present with disease-related decompensation [2,3].

In this regard, one of the best recommendations or Class I recommendations from scientific associations is cardiac rehabilitation (CR), which significantly improves adherence to treatment goals and survival in patients with HF [4,5]. CR programs improve quality of life and functionality and reduce long-term mortality by 20% to 30%. However, only 7.5% to 29% of patients are referred to and enrolled in a CR program, and only 40% to 55% of these patients can adhere to and complete treatment [6,7].

Lack of treatment adherence related to lifestyle changes and self-care is a factor that contributes to the occurrence of episodes of decompensation and hospitalization. This is reflected in the biomarkers and aerobic capacity measured through the 6-minute walk test [8]. Additionally, Poor health education, depressive symptoms, cognitive deficits, and multiple comorbidities may limit this low self-care capacity [6,9]. As a result, the low health literacy of HF patients translates into less knowledge about the disease, less self-care behaviors, deterioration of quality of life, and poor adherence to pharmacological and therapeutic treatment [9].

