### Sample

The population will include patients with a diagnosis of HF who will be admitted to a cardiac rehabilitation program in the city of Santiago de Cali, Colombia. It should be noted that this study aims to compare quantitative variables. Studies that compare means use the standard deviation as a measure of variation, so the variable of interest will be the distance covered in meters in the 6-minute walk test (6MWT).

The hypothesis of this study proposes that the group receiving telerehabilitation, telephone follow-up, and education will achieve better results in patients’ aerobic capacity, compared to the other experimental groups.

There are no studies with similar characteristics with telephone follow-up to obtain a walking distance equal to that of the telerehabilitation group. This is because the groups are homogeneous at the beginning of the intervention but heterogeneous at the end of the intervention program; 378.5 ± 96.9 for the conventional outpatient cardiac rehabilitation group and 432 ± 83 for cardiac telerehabilitation).

In turn, 95% confidence is estimated, error α: 5% (0.05), error β: 20% (0.20), power: 1-β: 80%, giving n = 46 participants for each experimental group, which is increased by 12% for possible problems in the measurements or dropouts of the study participants, so that n = 52 will be required and a total of 156 patients with HF per experimental group at the end of the study.

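### A place is freed after dropout in the telerehabilitation arms only, an arm-dependent rule acting after randomisation that can bias comparisons with conventional rehabilitation in a direction the protocol does not settle

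*Protocol article*

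**What the plan says.** The protocol article allocates by envelope: "Intervention allocation will be randomized using the block and sealed envelope method". In the same section it adds a rule for dropouts. The trigger is stated as "If a patient assigned to telerehabilitation drops out, unmasking will occur". The consequence is that "a place in the experimental group to which the patient belonged will become available, and the patient will continue the rehabilitation sessions as usual". The scope is then restricted: "This will be the case for those assigned to telerehabilitation". No counterpart is given for Group 2 (conventional rehabilitation).

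Four other places bear on this:

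- **Sample** sets 46 per arm, "which is increased by 12% for possible problems in the measurements or dropouts of the study participants", giving 52.
- **Reasons for stopping the intervention** withdraws patients with exercise problems from the study, whatever their arm.
- **Discussion** expects dropout above all in the conventional group, because those patients must travel.
- **Data collection, management, and analysis** names no analysis population. Its ANCOVA adjusts for age, sex and other confounders that reach the 5% level.

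**The concern.** Dropout happens after randomisation and can depend on both the assigned arm and the patient's prognosis. A rule that opens a place in response to dropout, in some arms and not in others, lets the make-up of those arms depend on who stays. If the place is filled and the patient who left is not counted in the assigned arm, Groups 1 and 3 drift towards people who persist with remote exercise, while Group 2 is handled differently. The difference from Group 2 in 12-week walking distance then mixes the treatment effect with selection. Covariate adjustment cannot be relied on to undo this, because the tendency to stay is not measured at baseline.

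The contrasts at stake are Group 1 with Group 2 and Group 3 with Group 2. Groups 1 and 3 share the rule, so the contrast between them does not suffer from the asymmetry.

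**Working it through.** **1. The plan's sample size.** Inputs from Sample: "378.5 ± 96.9 for the conventional outpatient cardiac rehabilitation group and 432 ± 83 for cardiac telerehabilitation" and "error α: 5% (0.05), error β: 20% (0.20), power: 1-β: 80". Sidedness is not stated; two-sided is assumed.

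- Difference: 432 − 378.5 = 53.5 m.
- Pooled SD: √((96.9² + 83²)/2) = 90.2 m.
- n per arm = 2(1.96 + 0.84)² × 90.2² / 53.5², which rounds up to 45. The t-test version gives 45.6, so 46 as stated. A one-sided test gives 36 and does not reproduce it.
- Allowance: 46 × 1.12 = 51.5, so 52; 3 × 52 = 156.

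The figures reproduce. A 12% loss from 52 leaves 52 × 0.88 = 45.8, in effect the planned 46, at which power is 81%. With all 52 analysed it is 86%. Within the loss the plan itself allows for, replacement is not needed to reach the planned size.

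**2. Size of a possible bias, no true effect.** The documents give no outcomes for dropouts, so this step rests on assumptions. Let a share q of a telerehabilitation arm drop out, be replaced by patients who stay, and not be analysed. Let ρ be the correlation between the tendency to stay and 12-week distance, under a normal model, and let Group 2 be fully observed. Then

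bias = ρ × SD × φ(z_q)/(1 − q),

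where z_q is the normal quantile for q and φ is the normal density. For q = 0.12, φ(z_q) = 0.200 and 0.200/0.88 = 0.227. The standard error of a two-arm difference at 46 per arm is 90.2 × √(2/46) = 18.8 m.

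| Assumed ρ | Bias (m) | Type I error at nominal 5% | Implied gap, stayers minus dropouts (bias/0.12) |
|---|---|---|---|
| 0.1 | 2.1 | 5.1% | 17 m |
| 0.3 | 6.2 | 6.2% | 51 m |
| 0.5 | 10.3 | 8.5% | 85 m |

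At ρ = 0.3 the bias is 6.2/53.5 = 12% of the planned difference.

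**3. Direction when Group 2 also loses patients.** If Group 2's dropouts are also left out of the analysis, the net bias is the telerehabilitation term minus the Group 2 term. At ρ = 0.3 the term is 6.2 m for 12% dropout and 11.5 m for 25%.

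- Equal dropout in both arms: 0 m.
- Telerehabilitation 12%, Group 2 25%: 6.2 − 11.5 = −5.3 m, against telerehabilitation.

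The Discussion expects the higher loss in the conventional group, so a zero or negative net bias is a live possibility.

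**4. If dropouts are analysed as randomised.** The selection bias in step 2 does not arise. If 12% of a telerehabilitation arm ended at the conventional mean, the expected difference would be 53.5 × 0.88 = 47.1 m, with power 76% at 52 per arm. That is dilution, and it works against telerehabilitation.

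**The case against.** The strongest reply is that much of the damage has to be inferred. The section says that a place becomes available; it does not say how the place is filled. It could go back into the envelope pool, and a person outside the research team conducts the draw. It does not define what continuing as usual means, nor say in which arm the patient is analysed. If all randomised patients are analysed as assigned, replacements mainly add sample size. These points stand, which is why the conclusion is conditional. They do not rescue the rule: a freed place has no evident purpose unless someone takes it, and the restriction to telerehabilitation is explicit.

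A reader might infer three stronger things, and the documents support none of them:

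- **That the rule favours telerehabilitation.** This needs Group 2 to be fully retained. The Discussion expects the opposite, and the withdrawal rule applies to every arm.
- **That the bias could reach 20 to 26 m.** The Introduction reports that "only 40% to 55% of these patients can adhere to and complete treatment", implying 45% to 60% non-completion. That describes cardiac rehabilitation in general. The large figures appear only if it is applied to telerehabilitation alone, with no loss in Group 2. Applied equally to both arms, the net bias in the same model is zero.
- **That the next allocation is foreseeable, or that dropouts are moved to in-person sessions.** Both are possible readings, but neither is stated.

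It is also fair to say that the 12% allowance covers measurement problems as well as dropouts, and that covering a loss twice is not in itself a bias.

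**Conclusion.** The point holds in conditional form. The protocol contains an explicit replacement rule, acting after randomisation and limited to Groups 1 and 3, and nothing in the document neutralises it. If places were refilled and dropouts are not analysed in their assigned arm, the contrasts with Group 2 are not protected by randomisation, and the sign of the bias cannot be read from the document. At the plan's own 12% loss, with Group 2 fully observed, the illustrated bias is modest: about 2 to 10 m for ρ between 0.1 and 0.5. It is smaller, zero or reversed once Group 2 also loses patients. These sizes rest on an assumed correlation and a normal selection model. The existence and asymmetry of the rule do not.

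**What to change.** Recruitment ended on 30/01/2025 (Study environment), so the remedy is mainly analytic.

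1. Remove the replacement rule from Assignment of intervention. Reconcile that section with Sample, with Reasons for stopping the intervention, and with the Discussion's expectation of dropout in the conventional group. State what continuing as usual refers to.
2. Make the primary analysis by assigned arm with all randomised patients, including those who left telerehabilitation. Seek their 12-week 6MWT where this is still possible.
3. Document every freed place: the arm, whether it was filled, and how the new patient was allocated.
4. Report results with and without any replacement not drawn by the ordinary envelope.
5. Treat completer or per-protocol results as supportive only.

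The clinical care of patients after dropout is unaffected. The cost is revised wording, a little extra follow-up and one additional analysis. The estimate may become less favourable, as the dilution example shows (47.1 m instead of 53.5 m under its assumptions).

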### Intervention

Prior to enrollment, patients will be seen in person for assessment of anthropometric data (height, weight, percent fat, water, muscle mass, and abdominal circumference), laboratory tests (total cholesterol, HDL, LDL, triglycerides, blood glucose, BUN), functional aerobic capacity (6MWT and sit-to-stand test), depression and anxiety questionnaires (HADS, Patient Health Questionnaire 9, PHQ-9), functional capacity (Duke Activity Status Index (DASI)), and health-related quality of life (HRQoL) Minnesota Living with Questionnaire MLFHQ [6]. These data will be collected again at the end of the 12-week intervention program.

The following is a detailed description of each intervention to be performed in this study, the assignment of the intervention according to the experimental group (Table 1), and the exercise prescription for each group (Table 2).

**Table 1 pone.0327366.t001:** Interventions assigned to each experimental group.

Arms	Intervention			
	Conventional rehabilitation	Education	Telerehabilitation	Telephone follow-up
Experimental Group 1		**x**	**x**	**x**
Experimental Group 2	**x**	**x**		
Experimental Group 3		**x**	**x**	

**Table 2 pone.0327366.t002:** Exercise prescription.

Arms	Exercise prescription
Experimental Group 1: Telerehabilitation, Education, and Telephone follow-up Experimental Group 3: Telerehabilitation and Education	**Devices:** Polar FT4 heart rate monitor to record heart rate and OMRON digital sphygmomanometer to monitor blood pressure. The conventional Borg scale (6/20) will be used. **Monitoring:** At the beginning of the session, patients will remain at rest in a seated position for 15 minutes. Heart rate and blood pressure will then be measured. Perceived exertion will be assessed using the conventional Borg scale. This measurement will be repeated during the strengthening and aerobic exercise and at the end of the session. **Intensity:** - Warm-up: To be performed with self-loading activities and position changes. - Central phase: - Strengthening: To be performed at 50% of RM, 3–4 sets for 12–15 repetitions. - Aerobic exercise: To be performed at 50% of HRmax, increasing the intensity every four weeks to a maximum of 70% of HRmax. If on beta-blocker medication, exercise will be prescribed to maintain perceived exertion between 11–13/20 on the Borg scale. - Cool down: To be performed at 50% of HRmax. If on beta-blocker medication, exercise will be prescribed to maintain perceived exertion less than 11/20 on the Borg scale. **Duration:** - Warm-up phase: To be performed for 10 minutes with self-loading activities and position changes. - Central phase: - Muscle strengthening for 20 minutes. - Aerobic exercise for 25 minutes. - Cool down phase for 5 minutes. **Frequency:** Three times a week for 12 weeks. **Professional assistance:** Via Google Meet by a physical therapist specializing in cardiac and pulmonary rehabilitation.
Experimental Group 2: Conventional rehabilitation and Education	**Devices**: This group will perform their intervention face-to-face in the cardiac rehabilitation program. They will use the clinic equipment. **Monitoring:** At the beginning of the session, patients will remain at rest in a seated position for 15 minutes. Heart rate and blood pressure will then be measured. Perceived exertion will be assessed using the conventional Borg scale. This measurement will be repeated during the strengthening and aerobic exercise and at the end of the session. **Intensity:** - Warm-up: To be performed with self-loading activities and position changes. - Central phase: - Strengthening: To be performed at 50% of RM, 3–4 sets for 12–15 repetitions. - Aerobic exercise: To be performed at 50% of HRmax, increasing the intensity every four weeks to a maximum of 70% of HRmax. If on beta-blocker medication, exercise will be prescribed to maintain perceived exertion between 11–13/20 on the Borg scale. - Cool down: To be performed at 50% of HRmax. If on beta-blocker medication, exercise will be prescribed to maintain perceived exertion less than 11/20 on the Borg scale. **Duration:** - Warm-up phase: To be performed for 10 minutes with self-loading activities and position changes. - Central phase: - Muscle strengthening for 20 minutes. - Aerobic exercise for 25 minutes. - Cool down phase for 5 minutes. **Frequency:** Three times a week for 12 weeks. **Professional assistance:** In-person by a physical therapist specializing in cardiac and pulmonary rehabilitation.

HRmax: Maximum Heart Rate

#### Telerehabilitation.

The program will be assisted by virtual technology. It will consist of performing exercises at home for 60 minutes three times a week for 12 weeks. The schedules for the telerehabilitation sessions will be agreed with the patients for their full participation. The exercises will be structured as follows: Warm-up, upper and lower limb muscle strengthening, continuous aerobic exercise, and return to rest. A cardiac and pulmonary rehabilitation physiotherapist will monitor the exercises via the Google Meet platform. This intervention will be carried out by experimental groups 1 and 3.

#### Telephone follow-up.

Telephone calls will be made three times per week (on days other than those assigned for telerehabilitation) as a follow-up method to obtain information from each person on heart rate and perceived exertion during home activities that they will be encouraged to perform outside of the intervention days. This intervention will be carried out by experimental group 1.

#### Conventional outpatient rehabilitation.

The program will be carried out in the cardiac rehabilitation program of the clinic. It will consist of physical exercises supervised by a physiotherapist specialized in cardiac and pulmonary rehabilitation for 60 minutes, three times a week for 12 weeks, structured as follows: warm-up, strengthening of upper and lower limbs, continuous aerobic training, and return to rest. This intervention will be carried out by experimental group 2.

#### Education.

It will be given once a week for 30 minutes to each patient individually and in groups. Topics will cover disease knowledge, medication use, warning signs, anxiety management, relaxation techniques, home exercises, sexual intercourse, and proper nutrition. This component will be delivered in person for experimental group 2 and virtually through the Google Meet platform for experimental groups 1 and 3. The meeting schedule will be arranged with all participants to ensure full availability for connection.

#### Reasons for stopping the intervention.

If, during the intervention, the patient experiences difficulty performing the exercise, symptoms of discomfort, angina, or changes in vital signs that interfere with the continuation of rehabilitation, the patient will be reassessed and withdrawn from the study.

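### Stopping exercise for symptoms also ends study participation, so 12-week outcomes are probably lost for reasons related to walking capacity

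*Protocol article*

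**What the plan says.** The section of the protocol article headed Reasons for stopping the intervention covers the case where "the patient experiences difficulty performing the exercise, symptoms of discomfort, angina, or changes in vital signs that interfere with the continuation of rehabilitation". The stated consequence is that "the patient will be reassessed and withdrawn from the study". The heading concerns the intervention; the consequence concerns the study.

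The Intervention section lists the baseline assessments (walk test, sit-to-stand, questionnaires, anthropometry, laboratory tests) and then says "These data will be collected again at the end of the 12-week intervention program". No other post-baseline assessment is described, and no follow-up is stated for patients who are withdrawn. What the reassessment consists of, when it takes place and whether it counts as an outcome are not stated.

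The sample size rests on 6-minute walk distance. The Sample section gives "giving n = 46 participants for each experimental group", "which is increased by 12% for possible problems in the measurements or dropouts of the study participants". This allowance is not divided by arm or by reason.

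**The concern.** Stopping exercise and leaving a trial are different events, and this rule makes the first cause the second. Its triggers are signs of poor exercise tolerance, which is close to what the walk test measures. Patients who leave under it would be expected, on average, to walk less far at 12 weeks than those who stay. The paired tests, ANOVA and ANCOVA in the data analysis section all need a 12-week value, so they would be run on a group selected for tolerating the exercise.

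Two results are at stake: the pre-post change within each arm, which would probably look too good, and the between-arm comparison, which could be distorted if withdrawal differs by arm. A later analysis plan can specify how missing values are handled, but it cannot recover measurements that the protocol stopped collecting.

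**Working it through.** **Inputs from the Sample section.** Distances are "378.5 ± 96.9 for the conventional outpatient cardiac rehabilitation group and 432 ± 83 for cardiac telerehabilitation". The difference is 432 − 378.5 = 53.5 m, and the pooled SD is √[(96.9² + 83²)/2] = 90.2 m. Alpha is 0.05 and power 80%.

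**Reproducing the plan's figure.** Two-sided, n = 2 × (1.96 + 0.84)² × 90.2² / 53.5² gives 45 per arm, and the t-test version gives 45.6, so 46. Then 46 × 1.12 = 51.5, so 52, and 3 × 52 = 156 in total. The stated size is reproduced. With the normal approximation, power is 81.2% at 46 analysed per arm and 85.6% at 52. The 12% allowance therefore protects precision. It does nothing against bias from who is lost.

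**Inputs not in the document (assumptions).** The share f withdrawn under this rule is taken as 5% to 20% per arm. The correlation ρ between exercise tolerance and 12-week walk distance is taken as 0 to 1, with 0.3 to 0.5 as the working range.

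**Shift in the mean of those remaining.** If the share f with the lowest tolerance leaves, the 12-week mean of the rest exceeds the mean of the whole arm by

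shift = ρ × SD × φ(z_f) / (1 − f),

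where z_f is the normal quantile at f. The factor φ(z_f)/(1 − f) is 0.1031/0.95 = 0.109 at 5%, 0.2000/0.88 = 0.227 at 12%, and 0.2800/0.80 = 0.350 at 20%.

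| Withdrawn | Conventional (SD 96.9), ρ = 0.3 / 0.5 / 1 | Telerehabilitation (SD 83), ρ = 0.3 / 0.5 / 1 |
|---|---|---|
| 5% | 3.2 / 5.3 / 10.5 m | 2.7 / 4.5 / 9.0 m |
| 12% | 6.6 / 11.0 / 22.0 m | 5.7 / 9.4 / 18.9 m |
| 20% | 10.2 / 17.0 / 33.9 m | 8.7 / 14.5 / 29.0 m |

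At ρ = 0 every entry is zero. The table concerns the 12-week mean. It carries over in full to the pre-post change if withdrawal is unrelated to baseline distance. If those who leave also walked less far at baseline, part of it cancels in the paired difference.

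**Change in the between-arm difference** (telerehabilitation shift minus conventional shift, planned difference 53.5 m):

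| Withdrawn: conventional / telerehabilitation | ρ = 0.3 | ρ = 0.5 | ρ = 1 |
|---|---|---|---|
| 12% / 12% | −0.9 m | −1.6 m | −3.2 m |
| 20% / 5% | −7.5 m | −12.4 m | −24.9 m |
| 5% / 20% | +5.6 m | +9.3 m | +18.5 m |

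With a common SD, the equal-rate row is 0 m. In the working range of ρ, unequal loss of this size moves the difference by 5.6/53.5 = 10% to 12.4/53.5 = 23% of the planned effect, with the sign set by which arm loses more.

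**The case against.** Several points on the other side stand.

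- The rule is narrower than a list of symptoms. It applies only where they interfere with continuing rehabilitation, so it may affect few patients. The triggers are also intolerance and symptoms, not a measured poor response.
- A reassessment precedes withdrawal, so some exit measurement may be taken. But nothing gives it content, timing or use in the analysis, so it cannot be counted as a 12-week outcome.
- The reason for leaving the program is already recorded (Clinical variables), so stops can be reported by arm without new data. That describes the loss but does not replace the missing outcome.

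A reader might infer that the bias is unequal across arms, because the conventional group is observed in person and the two telerehabilitation groups over video. The document does not support this as a fact. One withdrawal rule covers all arms, and Table 2 prescribes the same monitoring schedule for each, under a specialist physical therapist. Unequal loss is plausible: the Discussion expects more dropout in the conventional group because of travel, and Assignment of intervention describes unmasking and freeing of the place only for telerehabilitation patients. But no rate is given for any arm. If losses related to the outcome were heavier in the conventional arm, the telerehabilitation advantage would shrink rather than grow.

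A reader might also infer that the contrast between video and in-person observation threatens the telephone comparison. It cannot: by Table 1 that comparison is Group 1 against Group 3, and both are supervised by video. Group 1's extra calls, which ask about heart rate and exertion, offer more occasions to notice a problem, but the document does not say that they lead to withdrawal. It also gives no expected telephone effect against which to set a bias.

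**Conclusion.** The concern holds as a defect in an explicit rule. As written, patients who cannot continue the exercise leave the study before the only stated post-baseline assessment, for reasons likely to be related to the outcome. Each arm's pre-post change is probably inflated: by about 6 to 11 m at an assumed 12% withdrawn and a correlation of 0.3 to 0.5, less if those who leave also started with shorter distances. The between-arm comparison may be biased in either direction if withdrawal differs by arm: about 0 to 3 m at equal 12% rates, even with the correlation at 1, and about 6 to 12 m at an assumed 20% versus 5% with a correlation of 0.3 to 0.5.

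All of these sizes rest on assumed rates and correlations, and if withdrawal is unrelated to walking distance the bias is zero. Neither the presence of unequal bias nor its direction can be established from the document.

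**What to change.** Leave the clinical stopping criteria unchanged and change only their consequence for study participation. State that stopping the assigned exercise is not withdrawal from the study. Patients who stop remain in follow-up, have the 12-week assessments (questionnaires in all, the walk test where the treating clinician allows it), and are analysed in their assigned arm. State what the reassessment contains and whether any of it is used as an outcome. Report symptom-related stops by arm, and add a sensitivity analysis that assigns a poor value to those unable to walk.

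The cost is an amendment to the wording and a few extra visits or calls, using assessments the trial already performs. The sample size is unchanged.

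Timing limits what can be recovered. The Study environment section gives the end of recruitment as 30/01/2025 and planned completion as 20/06/2025; twelve weeks after the former falls in late April 2025. For patients already withdrawn whose 12-week window has passed, only the reporting by arm and the sensitivity analysis remain.
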